### Dose-response study

Following the time course study, sixty participants will be recruited for the dose-response study with placebo, 100 IU/day, 200 IU/day, 400 IU/day, 800 IU/day and 1600 IU/day natural (RRR) alpha tocopherol groups each consisting of ten people. If patients from the time course study agree to participate in the dose-response study they will undergo a 12-week period (wash out) where they will not be consuming alpha tocopherol. Dose-response study participants will be required to take two capsules per day (one in the morning and one at night) containing either a placebo or alpha tocopherol, to provide the respective IU/day doses.

The placebo will contain the emulsifying agent (wheatgerm oil) used in the alpha tocopherol supplement. Cognis Nutrition & Health Pty Ltd, Sydney, Australia, will supply all capsules.

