### Primary Objectives and Outcome Measures

The first primary objective is to determine the time point when oxidative stress is significantly reduced in haemodialysis patients taking 1600 IU/day of alpha tocopherol. Based on the Roberts et al. (2007) study in hypercholesterolemic patients, it is hypothesised that this will occur at 16-weeks [23].

Using this information, the second primary objective is to determine the optimal dose of alpha tocopherol required to reduce oxidative stress in patients undergoing haemodialysis. Based on the SPACE trial, it is hypothesised that ≥ 800 IU of alpha tocopherol will be required to significantly reduce oxidative stress [15].

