### Sample Size Calculation

The primary outcome measure for both studies will be the total plasma F_2_-isoprostane levels. For both studies, we will assume that the initial plasma F_2_-isoprostane levels will be 1600 ± 300 pg/mL. This is based on the inclusion criteria requiring patients to have plasma F_2_-isoprostane levels > 500 pg/mL, and also data showing plasma F_2_-isoprostane levels in haemodialysis patients were 1662 ± 289 pg/mL [24,25]. A decrease in plasma F_2_-isoprostane levels to 50% (800 pg/mL) of the initial values will be regarded as significant. To our knowledge, there is little data to support this assumption as no studies have assessed the relationships between plasma F_2 _isoprostanes and long-term health outcomes. Data from the Roberts et al. (2007) study found an approximately 50% reduction in plasma F_2_-isoprostane levels after 16 weeks vitamin E treatment in hypercholesterolemic patients [23]. With these assumptions, accepting their limitations and using a change variance of 350 pg/mL, with alpha = 0.05, beta = (1-0.1 = 0.9) we require five subjects per group. Assuming that five subjects per group will withdraw, die or receive a kidney transplant during the trial we will recruit ten subjects per group for both studies.

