### Statistical Analyses

The analysis of both the time-course and dose-ranging study will focus on analysing the changes in the levels of plasma F_2_-isoprostanes and alpha tocopherol, which occur during the intervention. The time-course study will use general linear modelling to analyse the levels of plasma F_2_-isoprostanes at bi-weekly intervals and levels of alpha tocopherol will be compared at baseline and week 20. In the dose-ranging study we will use general linear modelling to compare the changes in plasma F_2_-isoprostane levels between the intervention and placebo group at baseline and at the completion of the study. All statistical analyses will be performed using STATA statistical software (STATA 10; Statistical data analysis; Stata Corp; College Station; Texas, USA).

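### The dose-ranging analysis compares intervention with placebo, which does not answer the optimal-dose objective and could let non-significance at lower doses pass as evidence that at least 800 IU is needed

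*Protocol article*

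**What the plan says.** All references are to the Protocol article.

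- **Primary Objectives and Outcome Measures.** The second primary objective is to "determine the optimal dose of alpha tocopherol required to reduce oxidative stress in patients undergoing haemodialysis". The hypothesis is worded as a requirement: "it is hypothesised that ≥ 800 IU of alpha tocopherol will be required to significantly reduce oxidative stress".
- **Dose-response study (design).** Sixty participants form six arms: "placebo, 100 IU/day, 200 IU/day, 400 IU/day, 800 IU/day and 1600 IU/day natural (RRR) alpha tocopherol groups each consisting of ten people".
- **Statistical Analyses.** The one dose-ranging analysis is a general linear model of F2-isoprostane changes, compared "between the intervention and placebo group at baseline and at the completion of the study". The noun is singular. No comparison between doses, trend, dose-response model or rule for calling a dose optimal is attached to it.
- **Sample Size Calculation.** One effect size serves every arm. A fall in "levels to 50% (800 pg/mL) of the initial values will be regarded as significant", and "with alpha = 0.05, beta = (1-0.1 = 0.9) we require five subjects per group". Five losses per group are assumed, so ten are recruited.

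**The concern.** The objective asks a question about dose, and the stated comparison asks whether treatment differs from placebo. Two readings are possible, and neither answers the objective well.

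- **Pooled reading.** All active arms form one intervention group. The result says nothing about dose.
- **Five separate tests.** Each dose is tested against placebo. This shows which doses beat placebo, but it makes no use of the ordering of the doses. It also offers only one route to the claim that at least 800 IU is required: the lower doses are not significant.

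That route is weak because a lower dose with a real but partial effect may easily miss significance at this sample size. The dose and duration found here are meant to inform a large cardiovascular outcome trial, so a dose set by low power would carry forward.

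**Working it through.** **Inputs (Sample Size Calculation and the Dose-response study design).** Baseline 1600 pg/mL; target reduction 800 pg/mL; variability of change 350 pg/mL (called a variance, but in pg/mL, so read as an SD); alpha 0.05, taken as two-sided because sidedness is not stated; power 0.90; six equal arms; 10 recruited and 5 expected to complete per arm.

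**1. The protocol's own figure.** n per group = 2 × (1.960 + 1.282)² × 350² / 800² = 4.02, rounded up to 5. This matches. An exact t calculation gives 88.4% power with 5 and 94.5% with 6, so the stated figure is close. It covers one active group against placebo at the full 50% reduction, and nothing smaller.

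**2. Power for a partial effect.** In a six-arm linear model with pooled error, the SE of a dose-minus-placebo difference is 350 × √(2/n), with 6(n − 1) degrees of freedom.

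| Completers per arm | SE (pg/mL) | df | Power, 800 pg/mL | Power, 400 pg/mL | 400 pg/mL missed |
|---|---|---|---|---|---|
| 5 | 221.4 | 24 | 93% | 41% | 59% |
| 10 | 156.5 | 54 | over 99% | 71% | 29% |

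In a simple two-group t-test, the smallest difference detectable with 90% power is about 820 pg/mL with 5 per group and about 540 pg/mL with 10.

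**3. False dose claims.** If no dose works, five unadjusted two-sided tests against a shared placebo give at least one significant result in about 18% of simulated trials, with 5 or 10 per arm. (Independent tests would give 1 − 0.95⁵ = 23%.) Counting only significant reductions, the figure is about 9%, against a nominal 2.5%.

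**4. How often low power would seem to support the hypothesis.** The protocol gives no effect by dose, so the curves below are assumptions. In each, every dose truly lowers F2-isoprostanes and 1600 IU gives 800 pg/mL. The last two columns give the simulated chance that nothing below 800 IU is significant while 800 or 1600 IU is.

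| Assumed reduction at 100/200/400/800/1600 IU (pg/mL) | 5 per arm | 10 per arm |
|---|---|---|
| Linear: 50/100/200/400/800 | 75% | 71% |
| 320 at the three lower doses, 800 at the top two | 48% | 24% |
| Log-linear: 196/310/454/620/800 | 38% | 14% |
| Emax, ED50 200 IU: 300/450/600/720/800 | 17% | 2% |

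**5. Stability of the smallest significant dose.** For a further assumed Emax curve (200/333/500/667/800 pg/mL) with 5 per arm, the smallest significant dose is 100, 200, 400, 800 or 1600 IU in about 14, 21, 30, 23 and 9% of trials. A linear trend test across the six ordered arms has 98% power under the same curve. It establishes a dose relation but does not by itself choose a dose.

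**The case against.** The pooled reading rests on one singular noun in a condensed article. The protocol keeps six randomised groups, sizes each one, calls the study dose-ranging, and names general linear modelling, which can take dose as a factor or a trend. Contrasts and multiplicity handling are often left to an analysis plan, which is not shown. This stands in part. A reader might infer that the analysis cannot inform dose at all, but that is true only of the pooled reading. The missing multiplicity rule is not a finding in itself. What remains is that the comparison named for a primary objective does not answer that objective.

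A reader might also infer that low power would confirm the 800 IU hypothesis. The documents do not support that. All arms are the same size, so a lower dose achieving the full 800 pg/mL has the same 93% power with 5 completers. Under the Emax curve in step 5, a dose below 800 IU is the smallest significant one in about two thirds of trials, which contradicts the hypothesis. Nor does the protocol say that the dose will be picked by p-value; its one stated benchmark is the 50% fall, which it does not link to dose selection.

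Finally, the 18% should not be set against 2.5%: it counts increases as well as reductions. The like-for-like pair is 9% and 2.5%.

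**Conclusion.** The concern holds in a conditional form. The stated comparison does not match the optimal-dose objective. Under its more sensible reading, it leaves non-significance at 100 to 400 IU as the only support for the word required.

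The 59% and 29% miss rates for a 400 pg/mL effect follow from the protocol's own SD, with two-sided 0.05 and pooled error assumed. The frequency of false support (17 to 75% with 5 per arm, 2 to 71% with 10) rests on assumed curves and should be quoted only as a range. The low end shows that the problem can be small if the lower doses are nearly as effective as the top dose and few patients are lost.

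**What to change.** Replace the dose-ranging sentence in Statistical Analyses so that it states:

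1. A general linear or dose-response model over all six randomised arms (for example a trend on dose or log-dose, or a monotone or Emax curve), adjusted for baseline F2-isoprostanes.
2. The estimated reduction against placebo with a 95% CI at each dose.
3. That the optimal dose is judged on those estimates against the protocol's own 50% benchmark.
4. That non-significance at a lower dose does not show that the dose is ineffective.

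Do not use top-down testing that stops at the first non-significant dose as the dose-selection rule. It can only move the lowest claimed dose upward. With 5 per arm, the chance that 800 IU or more is the lowest claimed dose rises from 32% to 40% under the step 5 Emax curve, and from 0.6% to 8% when every dose gives 800 pg/mL.

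The cost is a little more analysis work and an assumption about the shape of the dose curve; no extra patients or samples are needed. The change does not create precision. Unmodelled arm-by-arm intervals would still be about ± 2.064 × 221.4 = 457 pg/mL with 5 per arm and ± 2.005 × 156.5 = 314 pg/mL with 10. It does make that uncertainty visible when the dose is chosen.

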## Discussion

Despite observational studies suggesting alpha tocopherol may protect from cardiovascular disease, most interventional studies have failed to support this contention. There may be many reasons for this discrepancy including the fact many patients treated in such studies may not have had elevated levels of oxidative stress. In addition, the administered alpha tocopherol may not have lowered oxidative stress. This time course and dose response study of alpha tocopherol in haemodialysis patients will provide data to support further large randomised controlled trials in this area.
